#### Recruitment {15}

Participants in Aim 1 will include educational staff, healthcare providers, parents, and children in the three regions participating in the study. The number of participants to be recruited will be based on the dual goal of reaching saturation and achieving representation of several different types of educational staff and healthcare providers, different regions, and different school sizes. Potential participants will be identified using purposeful and/or snowball sampling. Recruitment outreach will occur via email, flyers, presentations, and/or in-person, as appropriate. Informed consent procedures and study enrollment will be conducted by trained research staff. Children must have a parent/caregiver provide informed consent for a child to participate. In addition, children aged 7 to 17 years will be required to sign a child assent form. It is unlikely that a child under age 7 will participate. However, should a child younger than 7 years wish to enroll, then a verbal assent will be used in combination with parent/guardian informed consent.

Leaders in the Alaska Department of Education and Early Development will provide guidance to the study team on potential school districts that might participate in the randomized trial (Aim 2a). The study team will engage with superintendents in these districts to gauge interest. In participating regions, all students enrolled in grades that the district typically screens for hearing will be eligible for hearing screenings. Per standard practice, parents may opt out of school hearing screenings if they prefer their child not to receive screening. All students who receive a school hearing screening referral will be eligible for specialty telehealth follow-up (Years 4–5), but parent/caregiver consent will be required. Consent forms for the specialty telehealth follow-up will be included in routine annual school paperwork, or in other mediums based on guidance by the Community Advisory Board (CAB) and community input obtained during Aim 1.

Participants in the STAR model, including school staff, healthcare providers, and parents, will be engaged in questionnaires and interviews to evaluate implementation (Aim 2b). These individuals will participate as partners instead of consented research participants. Study staff will use email, phone calls, or in-person interactions to invite these partners to contribute. A participant information sheet will be provided to partners which emphasizes the voluntary nature of their contribution.

Relevant policymakers, state leaders, decision-makers in state government in healthcare, healthcare financing, and education; leaders of Tribal community and healthcare entities; and leaders of regional or local organizations that work on rural healthcare delivery will be recruited to participate in the sustainability evaluation of STAR (Aim 3). The sampling frame and specific leaders contacted to participate will be established through guidance from regional leadership and the CAB. Leaders will be recruited to participate as partners instead of consented research participants. A participant information sheet will be provided to partners which emphasizes the voluntary nature of their contribution.

We do not anticipate challenges with recruitment for the trial because data collection will occur at the population level, with entire schools participating. Individual consent will be obtained for the specialty telehealth follow-up intervention, and a community-informed implementation plan will be developed during the formative phase in Aim 1 to maximize uptake.

### Assignment of interventions: allocation

#### Sequence generation {16a}

Schools (n~25) will be randomized to one of two sequences using constrained randomization (49). Constrained randomization will be used to balance important baseline covariates between the two sequences in order to increase statistical power and improve internal validity of the trial. This will involve calculating a balance score for each allocation, incorporating into the balance metric candidate covariates expected to be correlated with the primary outcomes (chosen a priori by study team consensus), including: region, grades served by the school, hub school vs rural school, school enrollment (from 2022–2023 school year), proportion of students qualifying for free or reduced lunch, and baseline screening rate.

#### Concealment mechanism {16b}

Independent statisticians will perform the final randomization, and study statisticians will remain masked to allocation until the primary analysis is complete. The allocation cannot be masked for other study team members, school staff or parents for logistical reasons, but allocation will only be revealed when required.

#### Implementation {16c}

The independent statistician who performs the randomization will share the allocation with members of the study team responsible for implementing the intervention. Entire schools will participate in the trial; therefore, individual students are not enrolled or assigned to interventions.

### Assignment of interventions: Blinding

#### Who will be blinded {17a}

Statisticians will be blinded to allocation until primary analysis is complete. Allocation will only be revealed to study team members who require this information to manage the logistics of implementation at participating schools. School staff and parents will not be blinded to allocation.

#### Procedure for unblinding if needed {17b}

N/A. Families are not blinded..

### Data collection and management

#### Plans for assessment and collection of outcomes {18a}

The STAR model is comprised of enhanced hearing screening, specialty telehealth follow-up, and streamlined communication between schools, healthcare providers, and parents/caregivers. As described earlier, the enhanced hearing screening component of the intervention is based on prior evidence from our previous trial in Northwest Alaska and will not be randomized (27). As such, enhanced hearing screening will be implemented in all participating schools in Year 3 of the study, and Year 3 will be considered baseline for measurement of the primary effectiveness outcome. Specialty telehealth follow-up will be implemented in a stepwise fashion in Years 4 and 5 of the trial, with half of participating schools receiving specialty telehealth follow-up in Year 4 and all schools receiving it in Year 5.

The primary effectiveness outcome for the trial (Aim 2a) will be measured using annual queries of electronic health records (EHR) from the healthcare systems serving each region conducted (Table 1). We will engage with regional general medical centers, audiology practices, ENT practices, and Native health organizations in selected regions to gain a comprehensive understanding of clinical options available for follow-up care, and these regional sources will be included in the EHR queries. School screening data will be linked with queries from regional EHR and deidentified via a HASH ID process. Students with no record of receiving specialty care within 60 days of their date of screening will be considered not to have received follow-up care, as we will not be aware of students who move out of the region or receive follow-up care elsewhere. Based on our previous trial in Northwest Alaska, collecting EHR data for 60 days from screening date is sufficient to determine differences in rates of follow-up (25).

Secondary implementation outcomes (Aim 2b) will include fidelity, reach, acceptability, feasibility, and appropriateness (Table 1) (32). Fidelity will assess the extent to which core components of STAR are implemented as intended. Reach will assess the proportion of students reached by the STAR model. Acceptability, feasibility, and appropriateness will evaluate satisfaction with the STAR model and perceived fit of the intervention among participating school staff. Quantitative data sources for implementation outcomes will include trial process records, validated questionnaires, and school/regional-level data. Qualitative data sources will include interviews or focus groups with a subset of educational staff, healthcare providers, and parents participating in STAR. Qualitative interviews will occur annually during Year 3 (2023–24), Year 4 (2024–25), and Year 5 (2025–26) at the conclusion of school hearing screening (Figure 3). Specific measures used for each implementation outcome are detailed below.

Fidelity will be measured with structured checklists assessing adherence to the core components of the intervention. Individual components of the checklist will be designed during the formative phase. Fidelity of the telehealth specialty follow-up portion of the STAR model will also be evaluated by assessing time to specialty follow-up, comparing the date of specialty ear/hearing encounter to the date of screening. This measure will differ from the primary effectiveness outcome in that it will evaluate time to follow-up as a numeric variable rather than a categorical variable (i.e., follow-up within 60 days or not). Semi-structured interviews with educational staff, healthcare providers, and parents will be used to further explore contextual factors that influence variation in fidelity between schools. For educational staff, probes will be developed to ask about how various facets of the STAR intervention were used (i.e., which grade levels were screened, what screening tests were used, referral criteria, parental communication method). Similarly, for healthcare staff, probes may ask about whether follow-up care was completed using the telehealth interface developed for the STAR intervention.

Reach will be assessed annually via deidentified screening data from each region. This will include proportion of children screened using the STAR model by grade and school, focusing specifically on grades that typically receive screening in each individual school. We will also evaluate representativeness of children reached by the STAR model based on demographic factors such as race/ethnicity and region.

For acceptability, feasibility, and appropriateness, key informants will complete validated questionnaires, including Intervention Appropriateness Measure (IAM), Acceptability of Intervention Measure (AIM), Feasibility of Intervention Measure (FIM) (42), and Organizational Readiness for Implementing Change (ORIC) (43). Educational staff informants serving multiple schools will be asked to complete the survey for the region they are serving. Surveys will be completed annually to differentiate outcomes across various STAR components as they are rolled out. Annual qualitative semi-structured interviews with educational staff, healthcare providers, and parents will also be used to assess the acceptability, feasibility, and appropriateness of the intervention.

Sustainability of the STAR model (Aim 3) will be assessed qualitatively through iterative discussions with state leaders, policymakers, payors, and other relevant groups as well as through policy and procedural document review. From these discussions, we will identify key targets for policy and practice change and develop materials to support decisionmakers regarding these policy and practice changes.

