### Trial design {8}

The North STAR trial is a two-sequence, 4 period, stepped wedge, cluster-randomized hybrid type I effectiveness-implementation trial which will be conducted in 3 regions of rural Alaska (Fig. 3). The trial will evaluate the STAR model, which consists of three core components: 1) enhanced school hearing screening, 2) school-based specialty telehealth follow-up, and 3) streamlined communication between schools, healthcare providers, and families.

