#### Relevant concomitant care permitted or prohibited during the trial {11d}

As a pragmatic trial, we will not prohibit concomitant care. Parents and their children will be permitted to seek their own hearing care and arrange for follow-up or other interventions as they choose.

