**Secondary Outcomes**				
**Fidelity**	1. Adherence checklists 2. Time to specialty follow-up 3. Qualitative interviews	1. Final value (school) 2. Time to event (child) 3. Content analysis of qualitative data	1. Proportion of schools using STAR enhanced screening* 2. Median days to specialty follow-up from screening date 3. Contextual factors influencing fidelity between schools	Annually during Years 3–5
**Reach**	Children screened using the STAR model	Final value (school)	Proportion, overall and by race, ethnicity, region	Annually during Years 3–5
**Acceptability**	1. Acceptability of Intervention Measure (AIM) 2. Qualitative interviews	1. Final value (region) 2. Content analysis of qualitative data	1. Mean score 2. Themes	Annually during Years 3–5
**Appropriateness**	1. Intervention Appropriateness Measure (IAM)			
	2. Qualitative interviews			
**Feasibility**	1. Feasibility of intervention measure (FIM) and Organizational Readiness for Implementing Change (ORIC) 2. Qualitative interviews			
**Sustainability**	Sustainability of policies, payment, and infrastructure	1. Content analysis of qualitative data 2. Policy and procedure document review	1. Proposed policy targets for staff capacity, funding, and infrastructure 2. Materials to support decisionmakers	Years 3–5

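### The time-to-follow-up measure of telehealth fidelity measures effectiveness, not delivery of the telehealth session

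*Protocol article*

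**What the plan says.** The section Plans for assessment and collection of outcomes {18a} of the Protocol article states the construct: "Fidelity will assess the extent to which core components of STAR are implemented as intended". The Trial design section {8} lists the core components as "1) enhanced school hearing screening, 2) school-based specialty telehealth follow-up, and 3) streamlined communication between schools, healthcare providers, and families", so school-based telehealth is one of the things to which a school can be faithful.

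Section {18a} and Table 1 give fidelity three measures:

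- **Checklists.** "Fidelity will be measured with structured checklists assessing adherence to the core components of the intervention". Their content is deferred: "Individual components of the checklist will be designed during the formative phase". Table 1 analyses them at school level. Its one example metric concerns enhanced screening, and a footnote calls that metric illustrative.
- **Time to follow-up.** "Fidelity of the telehealth specialty follow-up portion of the STAR model will also be evaluated by assessing time to specialty follow-up". The interval runs from the screening date to a specialty ear or hearing encounter. The article distinguishes it from the primary outcome in that "it will evaluate time to follow-up as a numeric variable rather than a categorical variable". Table 1 summarises it at child level as "Median days to specialty follow-up from screening date".
- **Interviews.** Probes for healthcare staff may include whether the telehealth interface was used.

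Table 1 schedules the whole fidelity row every year from Year 3 to Year 5. Section {18a} and Table 2 put telehealth in no school in Year 3, in Sequence 1 only in Year 4, and in all schools in Year 5. On other care, section {11d} says: "Parents and their children will be permitted to seek their own hearing care".

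**The concern.** A fidelity measure for telehealth should register whether the telehealth session took place as planned. This one registers whether, and how soon, the child had specialty follow-up. Read as written, a visit that a family arranges at an audiology or ENT practice counts in the same way as a school telehealth session. The measure is also due in periods when a school has no telehealth to deliver.

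A hybrid type 1 trial relies on its implementation outcomes to explain its effectiveness result, and the Discussion says as much when it acknowledges difficulties with fidelity and uptake. Incomplete delivery is plausible. Telehealth needs parental consent, and the intention-to-treat population keeps children whose parents do not opt in. If the primary effect is small, this measure cannot tell whether sessions were not held or were held mainly for children who would have been seen anyway. If the effect is large, it credits self-arranged visits to telehealth fidelity.

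**Working it through.** The plan states no figure on this point, so there is none to reproduce. The check compares definitions, counts the schedule, and adds an illustration at the planning rates.

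**1. Event and time origin**

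| | Primary outcome | Fidelity item 2 |
|---|---|---|
| Start | Screening date | Screening date |
| Event | Specialty follow-up | Specialty ear or hearing encounter |
| Route required | None stated | None stated |
| Scale | Yes/no within 60 days | Days, summarised by the median |

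The scale is the only difference that the article states. That any encounter counts is an inference, from this wording and from the health-record sources of the primary outcome, which include regional audiology and ENT practices. The article does not say so outright.

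**2. Schedule**

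The layout over Years 3, 4 and 5, with 1 for telehealth, is Sequence 1: 0, 1, 1 and Sequence 2: 0, 0, 1.

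- Sequence-years without telehealth: 1 + 2 = 3 of 6, or 50%.
- School-years with telehealth = 2·n1 + n2, out of a total of 3·(n1 + n2).
- With 11 schools per sequence, as in the Sample size section: 2·11 + 11 = 33 of 66 with telehealth and 33 without (22 in Year 3 and 11 in Year 4).
- With 25 schools split 12/13: 37 of 75 with and 38 without. Split 13/12: 38 with and 37 without.

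The count uses the three years in Tables 1 and 2. The Trial design section speaks of four periods.

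**3. What an any-encounter result says about delivery**

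The Sample size section assumes 20% follow-up in the control condition and a 40-point increase, hence 60% under intervention. Let s be the share of referred children who are seen within 60 days only by another route. The article gives no value for s, so take the range 0 to 0.20, and assume that a telehealth session is itself recorded as specialty follow-up. Then the share reached by telehealth = observed share − s.

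- Observed 60%: 0.60 − 0.20 = 0.40 up to 0.60 − 0 = 0.60. Telehealth reached 40% to 60% of referred children, and between 0 and 0.20/0.60 = 33% of the counted events are not telehealth.
- Observed 20% (no effect): 0.20 − 0.20 = 0 up to 0.20 − 0 = 0.20. Telehealth reached nobody, or it reached 20% and replaced visits that would have occurred anyway.

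These are day-60 proportions. The planned summary is median days, so they illustrate the ambiguity and do not predict the reported statistic.

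**4. Other stated sources of delivery data**

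Checklists are analysed by school and their items are not given. Reach is the proportion of children screened, not the proportion who had telehealth. The interview probe is optional and qualitative. None of these is a stated child-level count of telehealth sessions.

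**The case against.** The strongest reply is that this measure is only a supplement. The article says telehealth fidelity will also be assessed this way. Under Strategies to improve adherence {11c}, the main instrument is a structured checklist completed by the research team and aligned with the implementation plan. The checklists address the core components, and telehealth is one of them. Trial process records are named as a further quantitative source. Leaving checklist items to the formative phase is no defect, least of all in a condensed article. This stands. A reader might infer that fidelity as a whole cannot show whether telehealth was delivered, or that use of the interface is covered only by an optional interview question. The article does not support either inference.

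A reader might also infer that the article gives one outcome two competing event definitions. It does not: it states a construct and then three measures of it, and it never defines a telehealth-session event for the time measure.

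Three further replies stand in part:

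- The Years 3–5 entry covers the whole fidelity row, and enhanced screening does run in every school from Year 3, so the schedule makes sense for the row. It does not make sense for a telehealth measure. Control-period times are a useful reference, but the comparison they allow is one of effectiveness.
- Numeric time carries information on speed that the 60-day outcome lacks, and timely access is the trial's stated purpose. The measure is therefore worth keeping, under another label.
- A school that looks like a control school is itself a warning sign. But it does not show whether sessions were missing or displaced other visits.

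**Conclusion.** The point holds for Fidelity item 2 and no further. Taken alone, that item is a rescaled effectiveness outcome: same event and time origin as the primary outcome, no required route, and a schedule that includes the 3 of 6 sequence-years without telehealth. It cannot separate delivery of telehealth from follow-up by other routes. The checklists and interviews may do so in part, but the article fixes no child-level quantitative measure of telehealth delivery.

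The 50% count needs no assumption beyond the three-year layout. The 33% is an upper bound that requires all self-arranged care to persist once telehealth is offered at school, and it should not be read as an estimate of misclassified events. The conclusion also rests on reading the encounter as one by any route, which is the natural reading but is not stated in so many words. The primary estimate, alpha and power are unaffected. The change should be made because it bears on how well the trial can explain its result.

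**What to change.** In section {18a} and in Table 1, Fidelity item 2:

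- Report the proportion of referred children with a completed STAR school telehealth session, and the days from screening to the audiologist's review of that session.
- Report both only for periods when telehealth is assigned: Sequence 1 in Years 4–5 and Sequence 2 in Year 5. That leaves 33 of 66 school-years at 11 schools per sequence, or 37 to 38 of 75 with 25 schools.
- Keep all referred children in the denominator, including those whose parents do not consent.
- Keep time to any specialty encounter in both conditions and all three years, labelled as a secondary effectiveness outcome.

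The cost is outcome-table wording and one field that marks school telehealth against other encounters, taken from the annual health-record query or from an export of the telehealth platform. The small downside is that this field must be carried through de-identification and linkage.

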#### Plans to promote participant retention and complete follow-up {18b}

Loss to follow-up is not expected to be not applicable for this study design, which involves a one-time, state-mandated school hearing screening and a one-time specialty telehealth follow-up for referred children. Follow-up data will be obtained from regional EHR queries with deidentification using HASH ID, thus reducing risk for loss to follow-up.

#### Data management {19}

The University of Arkansas for Medical Sciences (UAMS) will be the data coordinating center and will oversee data architecture and management. A secure research database will house all Aim 2a trial data from schools and healthcare entities. Data from other aims will be stored in password-protected, HIPAA-compliant cloud server hosted by Southcentral Foundation (SCF) and/or UAMS.

Schools in the participating regions will receive STAR model screening kits with telehealth capability. Schools will maintain their usual practice for tracking and managing school hearing screening results. All school and healthcare participant data will be deidentified via a HASH ID process prior to being shared with the research team. This HASH ID process will irreversibly remove identifiers (e.g., name, address) from the data while still allowing linkage of limited data sets from the school and healthcare systems. After this process, data will only be labelled by unique identification numbers. All data will be reported in aggregate, and no individual identifiers will be used in reporting.

Nearly all source documents will be electronic in nature and stored in cloud-based servers. All effort will be made to limit locally stored data, with copies backed up to secure servers and/or cloud-based solutions. Standard quality assurance measures will be carried out by the data manager and will be overseen by the Principal Investigators to ensure data quality and detection of erroneous data in accordance with the Data Safety Monitoring Plan (DSMP). Data quality control will be performed largely by the biostatistical team.

